### Informed consent

Eligible participants are provided with comprehensive information material, which includes the aims and procedures of the pilot study, data collection, and privacy policy by the participating medical institutions. If the eligible participants decide to participate in the pilot, they have to provide written informed consent to the Center for K-cospi as study subjects. The participants are informed that they can withdraw from the pilot study at any time for any reason. Data for subjects who withdraw from the study are discarded in a timely manner.

### Screening procedures and follow-up processes

The screening procedure is described in Fig. 1. Table 2 shows the SPIRIT schedule of enrolment, interventions, and assessment of this study protocol. At the participating medical institutions, bowel preparation medication is given to participants and a colonoscopy screening date is scheduled. All participants need to complete baseline questionnaires on demographics, current physical symptoms, past medical/surgical history, family history, CRC screening history, medication, and life style before colonoscopy screening.

**Fig. 1 Fig1:**
[figure not shown]
Flow chart of Korean colonoscopy screening pilot study procedure. *CRC* colorectal cancer

**Table 2 Tab2:** Schedule of enrolment, interventions, and assessments

Time point	Study period				
	Enrolment	Pre-treatment	Treatment	1-week follow-up	4-week follow-up
Enrolment					
Eligibility screen	X				
Informed consent	X				
Baseline questionnaire		X			
Interventions					
Bowel preparation		X			
Colonoscopy			X		
Assessments					
Telephone survey				X	X

The participants are asked to visit the medical institution on a scheduled date after their bowel preparation. Polyethylene glycol (PEG) 4L, PEG 2L, and oral sulfate solution are used as standard bowel preparation regimens in the study. All colonoscopies are performed by the participating endoscopists at each participating medical institution with or without sedation, according tothe preference of the participant. The local pathology labs or pathology labs within the participating medical institutions are responsible for tissue examination.

Endoscopists are responsible for follow-up workups or referral of participants for further investigations following their usual referral process, if necessary. Endoscopists need to provide detailed information to the Center for K-cospi on the screening results, results of additional workup, or details of referral if any.

The participants are informed to consult the hospital or visit the nearest emergency room if they experience any uncomfortable symptoms or complications after the colonoscopy procedure. The Center for K-cospi conduct a telephone survey twice—first within 7 days and the next within 4 weeks after colonoscopy—to collect data on any post-colonoscopy complications such as pain, bleeding, and perforations, which could have occurred and the level of satisfaction of the participants with the colonoscopy screening.

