**Methods:**

This study and its protocols have been approved by the Korean Public Institutional Review Board and the National Cancer Center Institutional Review Board. We obtain written informed consent from all participants. The target population is males and females aged 50–74 years living within the pilot sites. A total of 26,640 participants will be recruited for colonoscopy screening. Subjects who have been diagnosed with CRC, who are currently undergoing treatment for CRC, or who have undergone colonoscopy screening within the past 5 years are not allowed to participate. All participants need to complete baseline questionnaires. This pilot study is currently conducted by 104 endoscopists from 57 national cancer screening institutions (42 primary, 10 secondary, and 5 tertiary institutions) located in Goyang-si, Gimpo-si, and Paju-si. The number of endoscopists, medical institutions, and districts participating in the pilot study will be expanded, if necessary. Participating endoscopists at each medical institution perform colonoscopy and report the colonoscopy results to a centralized electronic case report system. We conduct a telephone survey after 7 days and 4 weeks post-colonoscopy to assess for procedure-related complications and satisfaction of the participants. In case of abnormal findings from colonoscopy screening, we track the results from follow-up diagnostic tests. Data from this pilot study will be linked to the diagnostic workup results, the Korean Cancer Registry, and death certificate data for analysis of the performance, long-term effects, and cost-effectiveness of colonoscopy.

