### Outcome measures

The primary outcomes for colonoscopy effectiveness are (1) the rate of detection of CRC and (2) the stage-shift effect of the colonoscopy procedure. The secondary outcomes are (1) major complications due to colonoscopy and (2) participant satisfaction and attitude towards colonoscopy screening.

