### Safety monitoring

The Center for K-cospi continuously tracks the occurrence of any immediate or delayed serious complications arising from colonoscopy depending on the information reported directly by the participating medical institutions or obtained from participants through telephone surveys. If we identify severe adverse events or unexpected admissions after colonoscopy, the Center for K-cospi requests a detailed investigation of the medical records from the hospital where the complications were treated. Moreover, it reports those events to the Monitoring Committee, Korean Public Institutional Review Board (IRB), and the National Cancer Center IRB. Early termination of the pilot study can be considered if the rate of severe adverse events is higher than expected, i.e.,1 cases per 1000 screening, 4 cases per 1000 screening, and 0.07 cases per 1000 screening for perforation, severe bleeding, and death, respectively. The Center for K-cospi has contracted an insurance to cover study-related harm.

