## Discussion

In this paper, we presented the objective, design, and study protocol of K-cospi. The present pilot study is planned to examine the effectiveness, complications, feasibility, and acceptability of colonoscopy as a primary method for CRC screening. FIT is provided free-of-charge as the primary CRC screening method through the NCSP in the Republic of Korea. However, their CRC screening rate was as low as 25% in 2012, and it was the lowest compared to their screening rates for other cancer types, such as stomach, liver, breast, and cervix [7]. In addition, a recent survey found that 68.7% of the participants would prefer the NCSP to adopt colonoscopy as its primary CRC screening test because it is accurate and can provide therapeutic options [6]. K-cospi was launched at an opportune time considering the low CRC screening rates of NCSP and the growing demand for colonoscopy by the national CRC screening program. Furthermore, this pilot study is of importance given that the lack of studies about the appropriateness of colonoscopy as the primary modality of CRC screening.

Previous studies have evaluated the efficacy and disadvantages of colonoscopy screening. A systematic review of observational studies of endoscopy demonstrated that the CRC incidence reduced by 69% (relative risk [RR] 0.31; 95% confidence interval [CI] 0.12–0.77) and mortality reduced by 68% (RR 0.32; 95% CI 0.23–0.43) [8]. Elmunzer et al. [9] found that colonoscopy was more effective than guaiac fecal occult blood test (gFOBT) (RR 0.49; 95% CI 0.30–0.76) in reducing CRC mortality. In addition, the detection rates for advanced adenoma with colonoscopy was significantly higher than those with gFOBT or FIT [10, 11]. However, the mortality rate within 30 days after endoscopy, major bleeding rate, and perforation rate were estimated to be about 1 in 15,000, 0.8 in 1,000, and 0.07–0.4 in 1000 procedures, respectively [12–15]. In other words, colonoscopy is vastly effective in screening for CRC but is highly risky at the same time. Therefore, it is important to evaluate the benefits of colonoscopy screening against its disadvantages in terms of efficacy, process, and cost. Cost is a decisive criterion for the implementation of a screening intervention [16].

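### The telephone survey for complications is timed in two incompatible ways, which leaves the observation period for major complications open, and the described safety sources are weak for the 30-day deaths behind the death benchmark

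*Protocol article*

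**What the plan says.** The timing of the telephone survey appears in three places in the protocol article.

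- Abstract, Methods: "We conduct a telephone survey after 7 days and 4 weeks post-colonoscopy to assess for procedure-related complications and satisfaction of the participants".
- Methods, Screening procedures and follow-up processes: two calls, "first within 7 days and the next within 4 weeks after colonoscopy".
- Table 2, in the same section: the survey is ticked under "1-week follow-up" and under a matching four-week column, with no permitted range of days.

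The survey feeds two things. Outcome measures lists "major complications due to colonoscopy" as a secondary outcome and states no period over which they are counted. Safety monitoring says that serious complications, immediate or delayed, are tracked "depending on the information reported directly by the participating medical institutions or obtained from participants through telephone surveys". Hospital records are requested once an event or an unexpected admission has been identified. The same section names rates per 1000 screenings above which early termination can be considered: 1 for perforation, 4 for severe bleeding and 0.07 for death.

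The only 30-day period is in the Discussion, where "the mortality rate within 30 days after endoscopy" is put at about 1 in 15,000 from the literature. Death-certificate linkage is planned under Data collection and management and under Data analysis plan. It is described for colorectal cancer incidence and mortality, with the long-term analysis after study completion.

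**The concern.** *After* sets an earliest date for a call and *within* sets a latest one. A site or call centre working from the Methods text could complete the second call in the second week and be compliant. From then on, no planned contact covers that participant. Rates per 1000 screenings would pool people observed for different lengths of time, and delayed complications would be the ones lost.

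Participants are told to consult the hospital or go to the nearest emergency room, which need not belong to a participating institution. For events treated elsewhere, the call is the main described route by which the study learns of them. Record review does not close the gap, because it starts only after an event has been identified. The error runs one way, making colonoscopy look safer than it is, in a study meant to inform a national screening decision.

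Deaths raise a separate problem. A call to the participant is a poor way to learn that the participant has died, whichever wording applies.

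**Working it through.** **1. The three timing statements side by side**

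| Place | First call | Second call | Earliest second call allowed |
|---|---|---|---|
| Abstract, Methods | after 7 days | after 4 weeks | about day 28 |
| Screening procedures, text | by day 7 | by day 28 | any day after the first call |
| Table 2 | 1 week | 4 weeks | not stated |

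The first two rows share only calls made exactly at day 7 and day 28. Table 2 fits either reading, though its column labels lean towards calls at about those times.

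**2. Can the loss be sized?** The document gives no distribution of onset times, so any figure is an assumption. For illustration, suppose onset within 30 days is exponential with mean *m* days and the last call falls on day *c*. The 30-day horizon is also an assumption for bleeding and perforation. The share of events starting after the last call is

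[exp(−c/m) − exp(−30/m)] / [1 − exp(−30/m)].

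| Last call | m = 3 | m = 7 | m = 14 |
|---|---|---|---|
| day 8 | 7% | 31% | 51% |
| day 14 | 1% | 12% | 28% |
| day 28 | 0% | 0.5% | 2% |

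These are shares outside survey coverage, not shares missed, because institutions also report directly. The range for early calls, 1% to 51%, shows that the document cannot settle the size. The bottom row shows that, under these assumptions, a call at four weeks largely removes the problem.

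**3. The death benchmark**

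- Benchmark (Safety monitoring): 0.07 per 1000.
- Cited 30-day mortality (Discussion): 1/15,000 = 0.067 per 1000, which rounds to 0.07. The benchmark is therefore reproduced by the 30-day figure.
- Expected deaths at the cited rate: 26,640/15,000 = 1.78.
- Deaths equivalent to the benchmark: 26,640 × 0.07/1000 = 1.86.
- One recorded death: 1/26,640 = 0.038 per 1000, below the benchmark. Two recorded deaths: 2/26,640 = 0.075 per 1000, above it.

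At full enrolment, recording one of two deaths instead of both moves the observed rate from above the benchmark to below it. Even a second call made exactly at day 28 stops two days short of the 30-day period to which the cited figure refers.

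**The case against.** The strongest reply is that *within* is loose wording. Table 2 has separate one-week and four-week columns and the abstract agrees with it, so two of three statements point to calls at about those times. This stands as a reading of intent. A reader might infer that both calls will in practice be made in the first few days; Table 2 argues against that. It does not remove the conflict, because the Methods text is the fullest description of the procedure and Table 2 sets no limits.

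Second, the survey is not the only source. Participating institutions report directly, and they number 57, including 10 secondary and 5 tertiary. This also stands. Missed late events and admissions are a risk, not a certainty.

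Third, the bleeding benchmark is far from the cited rate: 4 against 0.8 per 1000, a factor of 5. Moderate under-counting of bleeding would therefore be unlikely to alter an early-termination decision at rates near the cited one. This stands for the benchmark, though not for the reported secondary outcome.

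Fourth, deaths can be recovered through the planned linkage. They can, but no use of it for deaths after the procedure is described.

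A reader might also infer that unanswered calls bias the complication rates by a calculable amount. The document does not support that. It gives no response rate and no event rate in people not reached, the issue is the same under either call timing, and its handling may properly sit in the full protocol or analysis plan.

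**Conclusion.** The timing statements conflict and Table 2 does not resolve them. The Methods wording, followed literally, permits unequal and shortened observation for a secondary outcome that also feeds the early-termination rates. This is a risk of under-ascertainment in one direction, whose size cannot be estimated from the document.

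The weakness for deaths is a separate point and does not follow from the choice between *within* and *after*. It rests on the numerical match between the benchmark and the cited 30-day mortality, and on the sources that Safety monitoring describes. With fewer than two deaths expected, one unrecorded death matters.

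It would go too far to say that the protocol breaches a 30-day safety endpoint of its own. It sets none, and the 30 days attach only to the literature figure for mortality, not to those for bleeding or perforation.

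**What to change.** 1. Reconcile the abstract, the Screening procedures text and Table 2 into one call timing. Each call should be made at or after the end of the period it covers: the first not before day 7, the second not before week 4.
2. State one complication window, counted from the day of colonoscopy and the same for every participant, that the second call covers in full. Ask about that whole window at the call.
3. Use the planned death-certificate linkage to count all deaths within 30 days of colonoscopy, whether or not the call was answered, and report that count beside the 0.07 per 1000 benchmark.

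Items 1 and 2 cost wording and call scheduling. Item 3 adds a use to a linkage already planned; the sponsor should confirm that existing consent and ethical approval cover it. Linked deaths arrive later than telephone reports, so item 3 improves the final reported rate more than real-time monitoring. No new hospital or health-insurance linkage for admissions is proposed. The document does not plan one for complications, and it would not be a small change.

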### Data collection and management

The results of individual participants for the baseline questionnaire, colonoscopy, and pathology are stored in an electronic case report form on secure servers, which can be accessed only by authorized staff at the participating medical institutions. Participants areas signed a unique de-identified study ID and no personal information are stored in the electronic database. The centralized electronic case report form allows the Center for K-cospito continuously monitor the number of scheduled appointments, the number of completed screenings, colonoscopy results, and any missing, inadequate, or pending test results. All hard copy material collected at the participating medical institutions are routinely forwarded to the Center for K-cospi and kept in a secure cabinet. This includes the informed consent forms, screening questionnaires, pathology results, and spreadsheets containing personal information.

Data will be stored for a period of 15 years. For further analysis, the data will be linked to hospital medical records where diagnostic tests will be conducted, the cancer registry data of the Korean Central Cancer Registry, and death certificate data of the Korean National Statistical Office based on informed consent and ethical approval. This will be done to monitor the diagnostic workup, subsequent treatment, stage of cancer diagnosis, and CRC incidence and mortality during the 15 years of follow-up.

### Safety monitoring

The Center for K-cospi continuously tracks the occurrence of any immediate or delayed serious complications arising from colonoscopy depending on the information reported directly by the participating medical institutions or obtained from participants through telephone surveys. If we identify severe adverse events or unexpected admissions after colonoscopy, the Center for K-cospi requests a detailed investigation of the medical records from the hospital where the complications were treated. Moreover, it reports those events to the Monitoring Committee, Korean Public Institutional Review Board (IRB), and the National Cancer Center IRB. Early termination of the pilot study can be considered if the rate of severe adverse events is higher than expected, i.e.,1 cases per 1000 screening, 4 cases per 1000 screening, and 0.07 cases per 1000 screening for perforation, severe bleeding, and death, respectively. The Center for K-cospi has contracted an insurance to cover study-related harm.

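### The event rates called expected in the early-termination rule stand on different footings: 2.5 to 14 times (perforation) and 5 times (bleeding) the rates the protocol cites, but no margin for death

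*Protocol article*

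**What the plan says.** The Safety monitoring section of the protocol article allows early termination to be considered when severe events are "higher than expected, i.e.,1 cases per 1000 screening, 4 cases per 1000 screening, and 0.07 cases per 1000 screening", for perforation, severe bleeding and death in that order. No source is attached to any of the three. The same section says that complications are tracked continuously. Severe events and unexpected admissions lead to a request for a detailed record review, and these events are reported to the Monitoring Committee and both review boards.

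The Discussion gives the only other complication rates in the article. For 30-day death, major bleeding and perforation, in that order, they "were estimated to be about 1 in 15,000, 0.8 in 1,000, and 0.07–0.4 in 1000 procedures", with literature references.

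The number to be screened by colonoscopy is 26,640 (Abstract; Sample size calculation), and each person takes part once (Participant recruitment).

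**The concern.** A reader of the rule takes the three figures to be the complication rates that the investigators expect. Set against the Discussion, only the death figure can be that. The perforation and bleeding figures lie well above every rate the article cites, so they look like limits with a margin built in. The text does not say which figures are expected rates and which are limits.

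This matters because these are the only numerical triggers in the article, and complications are a stated secondary objective. A limit set at the expected rate will often be exceeded when nothing is wrong. A limit at several times the expected rate will, once the denominator is large, stay silent through a several-fold excess. One rule that does both gives the Monitoring Committee a signal whose meaning depends on which event raised it.

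**Working it through.** **Inputs.** Rule figures: 1, 4 and 0.07 per 1000 (Safety monitoring). Cited rates: perforation 0.07–0.4 per 1000, major bleeding 0.8 per 1000, 30-day death 1 in 15,000 (Discussion). Number screened: N = 26,640. Participants are treated as independent, and a limit counts as crossed when the observed rate is strictly above it.

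**Step 1. Can the rule figures be reproduced from the cited rates?**

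- Death: 1000/15,000 = 0.0667 per 1000, which rounds to 0.07. Reproduced; ratio 0.07/0.0667 = 1.05.
- Bleeding: cited 0.8, rule 4. Not reproduced; ratio 4/0.8 = 5.0.
- Perforation: cited 0.07–0.4, rule 1. Not reproduced; ratio 1/0.4 = 2.5 to 1/0.07 = 14.3.

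**Step 2. Limits as counts at N = 26,640.**

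| Event | Limit × N | Events needed to exceed | Events expected at cited rate |
|---|---|---|---|
| Perforation | 0.001 × 26,640 = 26.6 | 27 | 1.9 to 10.7 |
| Bleeding | 0.004 × 26,640 = 106.6 | 107 | 0.0008 × 26,640 = 21.3 |
| Death | 0.00007 × 26,640 = 1.86 | 2 | 26,640/15,000 = 1.78 |

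**Step 3. Like for like at full enrolment (exact binomial).**

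- Death at 1/15,000: P(0) = (14,999/15,000)^26,640 = 0.169 and P(1) = 0.301, so P(2 or more) = 1 − 0.169 − 0.301 = 0.530.
- Bleeding at 0.8 per 1000: P(107 or more) is about 7 × 10^-40. At three times that rate (2.4 per 1000, 63.9 expected) it is about 5 × 10^-7; at four times (3.2 per 1000, 85.2 expected) it is 1.3%.
- Perforation at 0.4 per 1000: P(27 or more) is about 2 × 10^-5.

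**Step 4. Crude rate checked after every participant.**

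A single event exceeds a limit L while n < 1/L.

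- Death: 1/0.00007 = 14,285.7, so one death exceeds the limit up to participant 14,285 (54% of N). P(at least one death by then) = 1 − (14,999/15,000)^14,285 = 0.614. P(limit exceeded at some point up to N) is 0.69.
- Bleeding: 1/0.004 = 250. P(at least one bleed in the first 249) = 1 − 0.9992^249 = 0.18. P(exceeded at some point) is 0.20 at the cited rate and about 0.60 at three times it.
- Perforation at 0.4 per 1000: 1/0.001 = 1000. P(at least one in the first 999) = 1 − 0.9996^999 = 0.33. P(exceeded at some point) is about 0.40.

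The at-some-point probabilities come from an exact recursion over the event count, participant by participant. For bleeding and perforation at the cited rates, nearly all or most of the probability arises while the denominator is small. For death it builds up over more than half of recruitment.

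**The case against.** The strongest reply is that the two sections need not agree. The Discussion reports approximate background rates from the literature and does not call them this trial's expected rates. It speaks of major bleeding and of death within 30 days of endoscopy; the rule speaks of severe bleeding, and of death without a window. A review limit above a published rate is no error in itself. All of that is fair, and whether the definitions match cannot be checked from the article. It does not explain perforation, which carries the same name in both places. Nor does it explain why the death figure has no margin when the other two have a large one.

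A reader might go further in three ways that the document does not support.

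- *That any single death triggers the rule.* This is true only up to participant 14,285. At full enrolment one death is 0.0375 per 1000 and two are needed.
- *That the rule is hair-trigger for death (69%) and blind to bleeding (below one in a million).* That contrast sets an at-some-point probability beside an end-of-enrolment one. On the end-of-enrolment basis the pair is 53% and about 5 × 10^-7. On the running basis, bleeding at three times the cited rate is flagged at some point with probability about 60%, although largely through early small denominators.
- *That participants are unprotected.* Crossing a limit allows termination to be considered and does not require it. Severe events go to the Monitoring Committee and the review boards whatever the rates.

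Finally, a condensed article commonly leaves the form of a statistical bound to the full protocol or a monitoring charter. Its absence here is not counted as a fault; what counts is that the published figures do not fit together.

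**Conclusion.** The point stands as an inconsistency in a stated decision rule. The figures described as expected are 2.5–14 times (perforation) and 5 times (bleeding) the article's own cited rates, and 1.05 times for death, which is rounding. At full enrolment, mortality exactly as cited exceeds its limit more often than not (53%), while a threefold excess of bleeding would almost never do so.

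These sizes assume that the cited rates apply to this population, that the events are defined alike in both sections, and that the observed rate is compared directly with the stated figure. The running-rate results also assume a check after every participant, which is one reading of continuous tracking. The ratios need only the matching of events.

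The primary outcomes and the sample size are untouched, the rule is permissive, and individual reporting runs alongside it. This is a should-fix. Which value is right for any event is not something this review can or should decide.

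**What to change.** Reconcile the Safety monitoring section with the Discussion. For each of the three events, state whether the figure is the expected rate or the review limit, give its source, and define the event (severity criterion for bleeding, time window for death). The Monitoring Committee should set the values.

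Once that is settled, judge the cumulative count against the agreed reference rate with an allowance for chance, for example by an exact binomial or Poisson bound, in place of a crude running rate. If a full protocol or charter already does this, a reference to it is enough.

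The cost is a short amendment and a little more monitoring work. No additional data are needed.
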